### Ethical consideration

Each study site will ensure ethical approval for each component of the study, according to local regulation. The study has already been approved by the following institutions: the Independent Ethic Committee of the University of Rome “Tor Vergata”; the Ethic Committee of the “Federico II” University of Naples, the Ethics Committee of the University Hospital in Valencia; the Medical Ethical Committee Twente; the IDIAP Jordi Gol Clinical Research Ethics Committee; the Regional Ethic Committee of Liguria; the ethics committee of the Regional Association of Health North (ARS North), and by each of the Associations of Health Centers in the region where data will be collected in Porto.

## Development of the program

The initial development of the ICP-PFM proposal over the first 12 months, is reported in Table 4: the first two sprints have already been achieved by 30 June 2016: a synthetic report on baseline assessment is in progress. The S4 sprint will be available by the end of 2016; it deal with the impact of the different interventions put in the field. This is a realistic picture of the aim of the whole proposal: to provide data about the effectiveness of Community-based intervention focused on frail citizens to reduce the negative outcomes of frailty itself and to contribute to both the sustainability of the health and social system and the equality of care opportunities (or at least procedures) throughout the EU countries.

## Conclusion

The synergy proposal is the result of sharing a pathway: assess the impact of community-based programs on the healthy and the use of services of community-dwelling older adults in order to select what is effective in terms of both reduction of costs for the providers of health services and negative outcomes for the individuals. The main goal is to scale-up of common approaches to mitigate the impact of frailty on community-dwelling older adults, by implementing a practical screening approach that allows early detection of frailty followed by strategies to manage frailty and functional decline. These approaches should reduce the incidence of adverse health outcomes in EU older citizens, who should improve their quality of life, and at the same time make health systems more efficient and sustainable. Finally these approaches include the implementation of new professionals and/or new models of care (including the implementation of ICT solution for better life) which encompass the collaboration among formal and informal carers: this is one way towards creating new opportunities for business that is the third component of the “triple win” boosted by the EIP-AHA [43].

## Figures and Tables

**Figure 1 f1-tm-15-53:**
[figure not shown]
Characteristic of frailty according to its domains and indicators.

* Total budget, in brackets: the budget obtained from the EU

**Table 3 t3-tm-15-53:** summary of the study design according to the implementation sites

Study site	Population^5^	Study design	Tools	Activities	Outcomes	Source(s) of comparison
Barcelona	Over 64 (1000 ind.s)	Prospective observational	-SFGE - RISC	-Frailty Pro-active screening/stratification and monitoring of community dwellers. -Referral to formal community-based or hospital-based services in case of need. - Community-based social activities including health promotion - Psychoeducational programmes for informal caregivers -Introduction of harmonised care bundles addressing multimorbidity, cognitive function and nutrition	Incidence of hospitalization Incidence of institutionalization Incidence of death	Official sources Data from different representative elderly cohorts in Catalonia, CARTS project in Cork, Porto and Galway. data stemming from the same sample according to a before-after interrupted-time series design
Cork	Over 64 (5000 ind.s)	- Prospective observational - Randomised trial (pilot)	-CFS -CARTS -RISC -SFGE	-Frailty screening/stratification -Targeted intervention	Incidence of frailty Progression of frailty Incidence of hospitalization Incidence of institutionalization Incidence of death	CARTS project in Galway
Galway	Over 64 1000 ind.s	Prospective observational	-CFS -CARTS -RISC -SFGE	-Pro-active frailty screening/stratification and monitoring -Introduction of a harmonised care bundle, common to the community-hospital interface (i.e. an integrated care pathway). -Referral to formal community-based or hospital-based services in case of need.	Progression of frailty Incidence of hospitalization Incidence of institutionalization Incidence of death	The CARTS project in Cork as a sister study. Retrospective data on older adults attending University Hospital Galway during the corresponding period one year before the interrupted time series study commences.
**Genova**	Over 64 (about 30 Individuals)	Prospective observational Randomised trial (pilot)	-SFGE -RISC	In particular, DOREMI activities include: early risk detection of : ○ malnutrition ○ cognitive decline ○ social isolation ○ sedentariness ○ falls early risk ICT intervention based on social nudges and gamification to the promote active and healthy lifestyle and behavioral in respect to the four main risk factors : change and maintain healthy nutrition lifestyle reduce social isolation change and maintain an healthy physical lifestyle train cognitive function and reduce cognitive decline	Progression of frailty Incidence of hospitalization Incidence of institutionalization Incidence of death	a) Official sources (report on the hospitalization and mortality in Italy and UK released annually by EUROSTAT, ISTAT etc.); b) Passi d’Argento report (Regione Liguria) b) Other sources (data stems from the ongoing project).
Naples	Over 74 (175 ind.s)	Prospective observational	-SFGE -RISC	-Pro-active frailty screening/monitoring -Assistance in bureaucratic tasks -Referral to formal community-based or hospital-based services -Strengthening the social involvement of pre-frail older adults -Community-based health and ICT literacy activities including health promotion -Introduction of assessment of polypharmacy regimen	Incidence of frailty Progression of frailty Incidence of hospitalization Incidence of institutionalization Incidence of death	Official sources (report on the hospitalization and mortality in Campania region released annually by ISTAT and Ministry of Health); data stems from the ongoing Lazio Region Frailty Study carried out by the University of Tor Vergata, Regional pharmaceutical Data flows (evaluation of polypharmacy)
Parma	Over 64 (1000 ind.s)	Prospective observational	-Sunfrail -SFGE -RISC	-Pro-active frailty screening of 1000 over-65 citizens followed by comprehensive geriatric assessments -Referral to day services or day-hospital-based services in case of need -Strengthening the social network around the frails -Activation of nutritional, physical exercise and technological monitoring interventions with specific targets: -Prevention of falls -Prevention of negative consequences of social isolation -Prevention of Malnutrition	Incidence of frailty Progression of frailty Incidence of hospitalization Incidence of institutionalization Incidence of death	Official sources (report on the hospitalization and mortality in Emilia Romagna region released annually by ISTAT and Ministry of Health);
Pecs	Over 64 (200 ind.s)	Prospective observational	-SFGE -RISC	-Frailty screening -training of the target group) on ICT skills -training of informal caregiver network on the use novel assessment and training tools. -widespan public awareness raising campaign of the general public in all participating countries	Incidence of hospitalization Incidence of institutionalization Incidence of death	official statistical data of the National Health Insurance and Statistical Bureau
Oporto	Over 64 (300 Ind.s)	Prospective double arm observational	- RISC	-A training program for PC professionals on frailty and dementia screening and intervention -A awareness program for the general community on frailty and dementia issues. -A psycho-educational program for caregivers of old people frail or with dementia. -A cognitive stimulation program for people with cognitive frailty or MCI	Incidence of hospitalization Incidence of institutionalization Incidence of death	Control group
Rome	Over 74 (4500 ind.s)	Prospective observational	-SFGE -RISC	-Pro-active frailty screening/monitoring -Home visits -Assistance in bureaucratic tasks -Referral to formal community-based or hospital-based services in case of need -Strengthening the social network around the frails -Community-based social activities including health promotion with specific targets	Incidence of hospitalization Incidence of institutionalization Incidence of death	Official sources (report on the hospitalization and mortality in Campania region released annually by ISTAT and Ministry of Health); data stems from the ongoing Lazio Region Frailty Study carried out by the University of Tor Vergata,
Salerno	Over 64 (100 ind.s)	two arms prospective observational	-SFGE -RISC	-Multidimensional assessment -Social and Health care integration -Electronic Clinical Record filled by the personnel and by the patient/caregiver -Home care monitoring and treatment by remote -Clinical management	Incidence of hospitalization Incidence of institutionalization Incidence of deaths	Control group
Twente	65–75 (300 ind.s)	two arms prospective observational	-GFI -SF-12 -SF-36 -MNA -SFGE -QMCI -NMA -Phys. test^6^	-frailty screening through multidimensional assessment -The PERSSILAA physical module Web-based exercising Monitoring	Incidence of frailty/functional decline Quality of LIfe	Control group
Valencia	Over 64 (1600 women)	Prospective observational	- Fried - CFS - SFGE - RISC	-Clinical assessments -Analytical Lab assessments -Bone metabolism assessment -Frailty assessment. -Cognitive frailty -Quality of life -Lifestyle intervention	Incidence of frailty Progression of frailty Incidence of hospitalization Incidence of institutionalization Incidence of death	pre and post-intervention assessment comparison with other cohorts within the working group (Twente)

**Table 4 t4-tm-15-53:** SPRINTS forecasted by the synergy proposal

N∘	Name	Starting date	Delivery date	Geographic coverage	Results
**S 1**	Set up a community - based public health approach to scale-up multidimensional screening tools in order to prevent, detect and manage frailty in community dwelling elderly. Target population and procedure to deliver the screening will be agreed. Ongoing interventions will be included into a common pathway defined by the assessment methodology.	15-Jan-2016	31-Mar-2016	Six Countries	Report on the action plan to implement a public health approach to frailty in community dwelling elderly and on the assessment methodology
**S 2**	Set up of a methodology to find out the impact of the public health program in this field It will be based on the agreement about the use of one methodology to assess frailty at baseline 12 and 24 months of observation (main candidate the RISC questionnaire – CARTS program), and to identifying common outcomes to be evaluated after 12/24 months of observation. Data will be gathered into one database that will be the main source of the evaluation. Comparative data will stem from official data source (mortality data, institutionalization rate, hospitalization rate, cost of services) which encompass the studied population. Specific observational cohorts could be included in local trials aimed to assess the impact of the interventions: this kind of approach could take longer than the first three months to be set up. Additional tools to assess specific aspects of the projects supporting the proposal, which are already used, could be included to improve the assessment methodology.	15-Jan-2016	31-Mar-2016	Six Countries	
**S 3**	Risk Classification of the first 20% of the sample About 200–400 citizens	1-Apr-2016	30-Jun-2016	Six countries	Report on the baseline assessment
**S 4**	First six months Impact assessment	1-Nov-2016	31-Dec-2016	Six countries	Report on the impact assessment on the citizens assessed before the 30 June 2016

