## Methodology of the ICP–PMF Synergy

### Study design

Prospective observational study. The results of the observation will be analyzed according to the observed/expected approach (indirect standardized ratio) with the same outcomes observed in the population matching the study population for age and sex distribution, and location of residence. The analysis will consider three approaches in order to compare the outcomes: a) pooling all together the citizens who underwent whatever intervention vs the ones who did not undergo interventions; b) compare who underwent both social and health intervention vs the ones who receive only social or health intervention and vs the ones who did not undergo intervention; c) assess the impact of specific intervention against a control group set up specifically for this purpose.

The sources of the comparison will be mainly data already available from established data-flow at international, national and local level. To give an example data on hospitalizations are largely available at national and local level and could represent the standard of care against the outcomes of the planned intervention could be compared. Studies utilizing this kind of data, carried out by stakeholders involved in this proposal are ongoing [35–36].

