### Sample size

– Alpha error = 5%– Power = 80%– Confidence Level = 95%– Confidence Interval = 1%– Population = 28,737,910^3^– Expected reduction of frailty incidence = 2.5%– Expected reduction of hospitalization rate = 5%– Expected reduction of Institutionalization rate = 5%– Expected reduction of death rate = 2.5%– Test 1 Proportion (observational study) superiority: sample size needed per single outcome = 2,000 subjects (including 10% of lost-to-follow up)^4^– Comparisons will be carried by applying the observed/expected approach on the basis of data stemming from the existing data flows available in the different study sites (national, regional or local data flow). The stratification of risk carried out by administering the baseline assessment will allow also transnational comparisons

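### The observed/expected framework and the one-proportion sample size treat the reference as fixed, but Table 3 gives several sites only or mainly finite comparators, most seriously Cork

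*Protocol article*

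**What the plan says.** The Study design section says that results will be analysed by the observed/expected approach, as an indirectly standardised ratio against a population matched on age, sex and place of residence. Three comparisons follow under that statement. The third is to "assess the impact of specific intervention against a control group set up specifically for this purpose". No other method of analysis is given for it.

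The Sample size section names one test: "Test 1 Proportion (observational study) superiority: sample size needed per single outcome = 2,000 subjects (including 10% of lost-to-follow up". Alpha is 5% and power 80%. The assumed reductions are 2.5% for frailty incidence and death and 5% for hospitalization and institutionalization, with no baseline rates shown. The same section bases the observed/expected comparisons on existing national, regional or local data flows.

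The Follow up section refers to Table 3 for the sources of comparison and adds that control groups of various kinds will also be used in some cases. Six rows of Table 3 name no official data flow:

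- Cork (5,000): only the "CARTS project in Galway".
- Galway (1,000): the Cork cohort and retrospective data on hospital attenders.
- Oporto (300), Salerno (100) and Twente (300): a control group only. Salerno and Twente are labelled "two arms prospective observational", and Oporto is described as double-arm.
- Valencia (1,600): pre/post assessment and the Twente cohort.

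**The concern.** A one-proportion test, or an observed/expected ratio with a fixed denominator, counts only the sampling error of the observed events. That is sound when the expected value comes from a whole region or country. A control arm or sister cohort has sampling error of its own. If this is left out, confidence intervals are too narrow, and a chance low or high rate in the comparator can be read as a programme effect. Enlarging the study site while the comparator stays small makes this worse.

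Cork and Galway show the conflict most clearly. Each is the other's reference, so each cohort would count as random when it is studied and as known when it supplies the expected value.

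The same mismatch affects the design figure: a sample size derived for a one-sample test does not carry over to a comparison of two samples.

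**Working it through.** **1. The stated sample size.** The 2,000 cannot be confirmed, because no baseline rate p0 is shown and the text does not say whether the reductions are absolute or relative. The one-sample formula is n = [z_a·√(p0(1−p0)) + z_b·√(p1(1−p1))]² / (p0−p1)². With a two-sided 5% test, 80% power, an absolute reduction of 2.5 points and an assumed p0 = 0.18, n = 1,790, and 1,790/0.9 = 1,989. An absolute 2.5-point reduction gives about 2,000 for p0 of roughly 0.175–0.19 (two-sided) or 0.24–0.26 (one-sided). The figure is therefore compatible with a one-sample calculation, as labelled.

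**2. Share of the sample (Table 3).** The twelve sites sum to 15,205.

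- Oporto + Salerno + Twente: 300 + 100 + 300 = 700 (4.6%)
- Adding Cork and Galway: 700 + 5,000 + 1,000 = 6,700 (44.1%)
- Adding Valencia: 6,700 + 1,600 = 8,300 (54.6%)

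**3. Error rate if the comparator is treated as fixed.** With n_t people studied, n_c in the comparator and equal event rates under the null, the true variance is (1 + n_t/n_c) times the assumed one. Actual two-sided error = 2·[1 − Φ(1.96/√(1 + n_t/n_c))].

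| Comparison | n_t/n_c | SE ratio | Actual error | Coverage of 95% interval |
|---|---|---|---|---|
| Control group, 1:1 (assumed) | 1 | 1.41 | 16.6% | 83% |
| Cork 5,000 vs Galway 1,000 | 5 | 2.45 | 42.4% | 58% |
| Galway 1,000 vs Cork 5,000 | 0.2 | 1.10 | 7.4% | 93% |
| Valencia 1,600 vs Twente 300 | 5.33 | 2.52 | 43.6% | 56% |
| 2,000 vs official source of 1,000,000 (assumed) | 0.002 | 1.00 | 5.0% | 95% |

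Simulation with event rates of 0.1 to 0.3 gave 42.3–42.5% for Cork vs Galway, 7.3–7.4% for Galway vs Cork, and 16.7–17.7% for 150 vs 150. For a one-sided test the figures are 12.2% (1:1) and 25.1% (Cork). The Valencia row can apply only to frailty incidence, because Twente lists no hospitalization, institutionalization or death outcome.

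**4. Pooled test over all sites.** With a 1:1 split, 350 of the 700 people at the two-arm sites are controls, leaving 15,205 − 350 = 14,855 studied.

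- Finite comparators at the three two-arm sites only: added variance 350/14,855 = 0.024, error 5.3%.
- Cork and Galway also used as each other's reference: the summed difference is (O_C − 5·O_G) + (O_G − O_C/5) = 0.8·O_C − 4·O_G. In units of p(1−p) its variance is 0.64 × 5,000 + 16 × 1,000 = 19,200, against 6,000 assumed, an excess of 13,200. Then (13,200 + 350)/14,855 = 0.912, and the error is about 16%.

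**5. Size of a two-sample comparison.** For the same absolute 2.5-point reduction at 80% power, before dropout, a two-sample test needs about 3,666 per arm (assumed p0 = 0.19, two-sided) or 3,634 per arm (assumed p0 = 0.255, one-sided). Taking 2,000 × 0.9 = 1,800 people as two arms of 900, power is about 28% and 34% respectively.

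**The case against.** The strongest reply is that the article never prescribes the one-sample test for control-group comparisons. The test is named once, under Sample size. There, observed/expected is tied to existing data flows, and Table 4 (S2) says that comparative data will come from official sources. Comparison with a dedicated control group is listed as a separate approach, and the Follow up section describes control groups as additional. The test for a two-arm contrast may stand in an analysis plan that is not shown.

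This stands as far as it goes: the excess error is conditional. It does not remove the conflict. The Study design section puts all three approaches under observed/expected, and Table 3 leaves Cork, Oporto, Salerno and Twente with no reference other than a finite one, so those comparators are not additional to anything listed.

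A reader might infer that false positives will far exceed 5% at sites with over half the sample. The documents do not support that, for three reasons. Nothing says that these comparators will be analysed as fixed. Over half is reached only by counting Valencia, whose first listed comparison is pre/post. And the inflation is uneven: Galway against Cork reaches only 7.4%, and Galway also lists retrospective hospital data. The Salerno and Twente rows together hold 400 people (2.6%). Cork also lists a pilot randomised trial, which a proper two-group analysis could serve, although Table 3 names only the Galway cohort as its comparator.

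**Conclusion.** Wrong as written. A fixed-reference analysis and a one-sample size calculation are stated for the study as a whole, while Table 3 gives only finite comparators at Cork, Oporto, Salerno and Twente and mainly finite ones at Galway and Valencia.

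The more certain defect is the scope of the design figure: 2,000 subjects with 80% power does not cover two-sample comparisons. The error-rate consequence follows only if the stated framework is applied to these comparators. It would then be serious at Cork, moderate at the two-arm sites and small at Galway against Cork. A pooled result would be affected mainly through Cork.

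The figures assume a 1:1 split at the two-arm sites, Table 3 numbers as the numbers analysed, equal event rates under the null and no clustering. The power figures also rest on assumed baseline rates and an absolute reading of the 2.5% reduction.

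**What to change.** In the Study design and Sample size sections:

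1. Restrict observed/expected with a fixed reference to sites whose expected values come from official population rates.
2. Where the comparator is a control group or another cohort, use a two-sample rate ratio, for example Poisson regression with group, age and sex. Alternatively, add the comparator's variance to the interval: Var(log ratio) = 1/O + 1/O_ref, where O_ref is the number of events in the comparator. Cork and Galway then form one two-sample comparison, not two separate ones.
3. State that the 2,000-subject, 80% power figure applies only to comparisons with a fixed population rate.

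This changes wording only and needs no new data. The cost is wider intervals at the affected sites and a less favourable statement of power for their comparisons.

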### Sample

Subjects for inclusion/assessment will be aged over 64 years and living at home; those living in an institution (nursing homes or similar) will be excluded. Each study site can decide to restrict the field of intervention with additional exclusion criteria. The total number of European citizens involved in the assessment will be around 2000 for each outcome of which at least 20% will be enrolled before the end of June 2016.

Participants will be enrolled among the ones who access the services managed by the stakeholders involved in the proposal. In Ireland, participation in the study will be offered to community-dwelling older adults who are under surveillance by their Public Health Nurse consistent with ongoing studies in this setting [10, 13, 14]; in Valencia participant will be the women who access the outpatients department of the University Hospital gynecologic service for health control. In Genoa participants to the DOREMI project will be enrolled enrolled involving citizens who access to the local University Hospital. In Barcelona participants will be enrolled among communitydwelling older adults who are attended by their primary health care team, both in the office and at home. In Twente and Campania, community dwelling older adults will be enrolled among participants to the PERSSILAA project, patients referring to Federico II outpatients practices and to the GPs of the Salute in Collina no profit organization. Campania study sample will also include participant to the Sunfrail pilot, and to the Beyond Silos project in Salerno. In Rome the over-74 citizens reached by the Viva gli Anziani program (all living in the community) will be included in the study. In Porto participants will be primary care patients of Health Centers that agreed to participate. People over 64 years will be prescreened by trained GPs and further assessed by the CARTS project team, supported by the General Directorate of Health. In Parma the over 64 citizens of Central District of Parma will be included as part of Sunfrail and SprinTT recruitment process. In Pecs community dwelling older adults will be enrolled from members and clients of local NGO’s Wherever possible the General Practitioner of the citizens involved in the study will be informed.

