### Follow up

According to the different program/projects intervention schemes, follow up data will be gathered every six-twelve months. The follow up will consist of the information that will be obtained following the baseline assessment on incidence of frailty, hospitalization, institutionalization and death. The study will run for 36 months in total including three months set up time and three months at the end to finalize the assessment (Fig 2)

Table 3 reports the list of study site with the list of data sources to be considered in the study for the comparisons. In some cases different kind of control groups will be also used: historical or ongoing cohort of citizens, assessed for frailty with comparable tools, who did not underwent any intervention will be involved in the data analysis. Data will be analyzed every six months

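### Sprint S4 observes April to December only, and expected counts are not matched on calendar period; where yearly official rates supply them, a winter peak would modestly lower observed/expected with no true effect

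*Protocol article*

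**What the plan says.** **Dates.** In Table 4, S3 runs from 1 April to 30 June 2016: "Risk Classification of the first 20% of the sample About 200–400 citizens". The Sample section agrees on the cut-off: "at least 20% will be enrolled before the end of June 2016". S4, the "First six months Impact assessment", starts on 1 November, is due on 31 December 2016, and yields a "Report on the impact assessment on the citizens assessed before the 30 June 2016". The Development section adds: "The S4 sprint will be available by the end of 2016; it deal with the impact of the different interventions put in the field". The Follow up section says "Data will be analyzed every six months".

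**Comparison.** The Study design section sets observed against expected outcomes by indirect standardization, using a "population matching the study population for age and sex distribution, and location of residence". Calendar period is not among the matching variables. Comparators are to be mainly existing data flows.

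**Sources in Table 3.**
- Parma names only a "report on the hospitalization and mortality in Emilia Romagna region released annually by ISTAT and Ministry of Health".
- Genova, Naples and Rome name similar annual reports, each with at least one other source.
- Oporto, Salerno and Twente name control groups.
- Galway names retrospective data for the same stretch of the previous year.
- Barcelona adds an interrupted time series.

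**Later evaluation.** Under S2, Table 4 foresees common outcomes evaluated at 12 and 24 months.

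**The concern.** A yearly rate averages all four seasons. A cohort entered from April to June and reported by December contributes only to the last three quarters. If hospitalization and death among older people are commoner in winter, halving a yearly rate gives an expected count that is too high for this window, and O/E falls below 1 with no programme effect. Standardizing for age, sex and residence cannot remove this, because season is a property of the follow-up window and not of the people.

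With any January-March peak the direction is known: it favours the programmes. It also acts alike at every site that uses yearly rates, so pooling those sites does not average it out. S4 matters because the article presents it as reporting impact and as illustrating the purpose of the whole proposal.

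**Working it through.** The documents give no seasonal figure and no baseline rate, so there is no figure in the plan to reproduce on this point. The size is computed over an assumed range.

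**1. Person-time.** Entry is taken as uniform over 1 April-30 June 2016, with follow-up ending by 31 December at the latest. The share of person-time in January-March is 0%.

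**2. Cosine seasonality (assumption).** Rate = mean × [1 + A·cos(2π(t − peak)/365.25)], peak in mid-January, true effect zero, expected counts from the annual mean. With six months of follow-up each, the fall in O/E is A times the product of:
- averaging over 183 days: sin(π·183/365.25)/(π·183/365.25) = 0.635
- averaging over 91 entry days: sin(π·91/365.25)/(π·91/365.25) = 0.901
- average mid-window in mid-August, about 212.5 days after the peak: cos(2π·212.5/365.25) = −0.871

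0.635 × 0.901 × 0.871 = 0.498; day-by-day summation gives 0.497. Summation gives 0.600 for follow-up to 31 October and 0.258 to 31 December.

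| Fall in O/E under no effect | A = 5% | A = 10% | A = 15% |
|---|---|---|---|
| Six months each | 2.5% | 5.0% | 7.5% |
| To 31 October (S4 start) | 3.0% | 6.0% | 9.0% |
| To 31 December (S4 due) | 1.3% | 2.6% | 3.9% |

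Moving the peak anywhere from mid-January to mid-February changes the factors to 0.50-0.57, 0.60-0.65 and 0.26-0.41.

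**3. A different shape (assumption).** Let January-March run x above the annual mean, with the rest of the year flat. The fall in O/E is x·91/275 = 0.331x. A 2.5% fall needs x = 0.025/0.331 = 7.6%; a 5% fall needs 15.1%.

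**4. Against the effects sought.** The Sample size section gives 5% for hospitalization and 2.5% for death, without saying whether they are relative or absolute. Read as relative, they lie within the range above. Read as absolute points, 2.5 and 5 points are 12.5% and 25% of a 20% yearly rate, or 25% and 50% of a 10% rate, and the shifts in the table do not reach them. The stated 2,000 does not settle the reading. For 1,800 evaluable subjects in a two-sided one-proportion test, an absolute 2.5-point fall needs a baseline near 18%, and a relative 2.5% fall one near 88%. An absolute 5-point fall never needs more than 783.

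**5. Against chance.** Expected events in six months = n × yearly rate / 2, and SE(O/E) ≈ 1/√E. With 200 people at an assumed 5% rate, E = 5 and SE = 45%. With 400 at 30%, E = 60 and SE = 13%.

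**6. Reach.** Genova, Naples, Parma and Rome hold 30 + 175 + 1,000 + 4,500 = 5,705 of the 15,205 people in Table 3 (37.5%); Parma alone holds 1,000 (6.6%). If S4 mirrored Table 3 and only these four sites used yearly rates, six-month shifts of 2.5/5.0/7.5% would dilute to about 0.9/1.9/2.8% in a pooled O/E.

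**7. Later analyses.** Thirty-six months less three for set-up and three for closing leaves 30. From April 2016 that is two whole years plus one extra April-September. For a participant followed throughout, null O/E is 0.994/0.988/0.982, a shift of 0.6/1.2/1.8%. Over exactly 12 or 24 months the cosine averages to zero.

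**The case against.** The strongest reply is that no sentence says expected counts will be scaled from a yearly rate. Annual release describes how often a report appears, not the resolution of the data behind it, and aligning person-time with reference periods is detail an article may leave to its analysis plan. This stands in part and makes the point conditional. It does not dispose of it: the article fixes the S4 window and lists the matching variables, and calendar period is not among them. Galway's comparator shows that the consortium has season-matching available.

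A reader might go further and infer that S4 will show a false reduction as large as the one sought. The documents do not support that:
- The seasonal amplitude is an assumption.
- The 2.5% and 5% may be absolute.
- Only Parma rests on annual reports alone.
- Season largely cancels at Oporto, Salerno, Twente and Galway, and in the planned contrasts of treated with untreated citizens if these run concurrently.
- With 200-400 people, a standard error of 13-45% hides a shift of a few percent.
- A winter peak is less evident for institutionalization and frailty incidence.

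It is also fair that S4 is a progress report with no decision rule attached, and that the 12- and 24-month evaluations already cover whole years. What survives is that imprecision does not excuse a tilt whose direction is known in advance and which is cheap to remove.

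**Conclusion.** The point holds as a modest, conditional bias in S4 and in other six-monthly analyses that do not span whole years. It rests on the Table 4 dates, on matching that omits calendar period, and on two assumptions: that some sites derive expected counts from yearly rates, and that hospitalization or death peaks in winter. With an amplitude of 5-15% and a mid-January peak, O/E at those sites falls by about 2.5-7.5% with six months each, or 1.3-3.9% with follow-up to 31 December. That is of the order of the effects sought only if they are relative. The shift is below chance error in S4, shrinks to 0.6-1.8% over 30 months, and vanishes over whole years.

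**What to change.** State that, in S4 and every six-monthly analysis, expected counts are computed from reference rates for the same calendar months as the participants' person-time. Rates for those months in the same year are preferable. The same months of an earlier year also remove the seasonal tilt but leave year-to-year variation. Where a source offers only yearly rates, make impact statements only on whole 12-month periods per participant, and limit S4 at those sites to describing baseline risk and completeness of follow-up. Say also whether the 2.5% and 5% are relative or absolute, so that any remaining bias can be judged against them.

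The cost is a request to the same data holders for monthly tabulations. Where these cannot be had, the first impact statement at those sites moves from the end of 2016 to mid-2017, a delay of about six months. No extra participants or visits are needed.
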